### Intervention

The physicians in each intervention network will receive feedback sheets and be invited by their respective Regional Associations of SHI Physicians to take part in a series of four voluntary network meetings. The meetings will take place in months 3, 9, 15 and 21 of the intervention. The invitations will be sent out before each meeting and followed by one reminder in cases where no reply is received. In total, the physicians will be sent eight feedback sheets. These will be sent out at least 2 weeks before each meeting. The meetings will be led by a trained facilitator. The 2-year intervention will take place from late 2018 to late 2020. (Addendum October 2020: Due to the COVID-19 pandemic beginning in early 2020, we had to cancel all network meetings between March and May 2020. The meetings were resumed in June 2020 and will be held until January 2021). Figure 2 summarises the study design, intervention and methods of the ACD study.

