The secondary outcome will be rates of treatment provided in accordance with the relevant clinical practice guidelines. Treatment in this context will be defined as (a) the type and amount of medication prescribed by physicians in the networks, (b) whether regular follow-up visits have taken place and (c) whether the physicians follow the recommended diagnostic procedure [15–19].

Both the primary and secondary outcomes will be calculated based on the routine data described above and evaluated at baseline, at the end of the 2-year intervention period, and at 6 months and at 12 months after the end of the intervention period. The outcomes will be evaluated using an intention-to-treat approach within multi-level models [20].

Additionally, in accordance with MRC guidelines [21], we will undertake a process evaluation and a cost-effectiveness analysis. Through the latter, it will be possible to evaluate how changes in the relevant medical effects of the intervention are related to changes in its costs [22]. The analysis will take account both of additional costs from the perspective of the statutory health insurers (payer perspective) and the marginal effects of hospitalisation rates among the intervention networks compared to those among the control networks. This information will be used to discuss the potential to implement the intervention to other contexts within Germany [21].

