The process evaluation will combine qualitative and quantitative approaches to identify potential causal factors, as well as enablers of and barriers to the acceptance of feedback and the implementation of facilitated network meetings throughout the study. Initially, all 60 facilitators will have to complete a questionnaire on their expectations of and satisfaction with the ACD-specific training they receive. After each network meeting, participants and facilitators will be asked to fill in a questionnaire to reflect on the meeting and their personal experiences of the ACD study. Additionally, 36 semi-structured telephone interviews will be held with facilitators and randomly selected physicians who give consent to be contacted. After receiving at least two network information sheets, participating physicians will be offered the chance to give feedback on the layout and content of the network information. Finally, coordinators from the Regional Associations of SHI Physicians, who were responsible for organising the network meetings, were asked for written feedback on important organisational aspects of the intervention and for lessons learnt during the study.

(Addendum October 2020: Due to the COVID-19 pandemic and the resulting cancellation of meetings between March and May of 2020, all physicians from the intervention group received a questionnaire for them to assess the intervention, including questions on their satisfaction with the feedback sheets and organisation of network meetings and to make suggestions for improvement.)

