### Randomisation and sample size estimation

Among the networks identified in the data set described above, we will select a random sample of 100 intervention and 100 control networks. These networks will be divided into strata according to (a) the four regions covered by the Regional Associations of SHI Physicians and (b) whether they are located in an urban or rural area, as it can be assumed that the structure of the networks will differ depending on their location, which, in turn, will have an impact on the measured outcomes [23]. Within these strata, the networks will be randomised to the intervention and control groups with equal size [24]. Networks of the strata will be randomly assigned to the intervention or control group by statisticians of the Hannover Medical School using the software nQuery 7.0. The statisticians are not otherwise involved in the planning of the study design. Sequence allocation and assignment is conducted based on the network identifier (generated by the study group) without information on physician identities.

The sample size estimation based on the assumption of a 20% hospitalisation rate and a 15% reduction in ACSHs following the intervention, we thus expect a 17% ACSH rate in the intervention group. The numbers were chosen after reviewing comparable studies and analysing hospital routine data [14, 25, 26]. With a 5% significance level and a power of 80%, 2629 patients per group would be needed to show this effect (2-sided *χ*^2^ test). For cluster-randomised studies, the estimated sample size must be adjusted by the design effect, which is a function of cluster size and the intracluster correlation coefficient (ICC). Assuming an ICC of 0.015 [27] and an average of 300 patients per network yields a design effect of 5.485. This means that the estimated number of cases of an individual-randomised study has to be multiplied by 5.485. With this design effect, 28,840 patients and thus 96 networks per arm (intervention and control) will be needed.

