As described above, the intervention networks will receive feedback sheets and be invited to facilitated network meetings by the Regional Association of SHI physicians. According to Section 287 of Book V of the German Code of Social Law (§ 287 SGB V) the regulatory authorities confirmed that Regional Associations of SHI Physicians may send the feedback sheets to their members without prior written, informed consent by the office-based physicians (please see section on ‘participant consent’). Participation in the informal network meetings will, however, be voluntary. Data will be analysed using an intention-to-treat approach, with all office-based physicians who receive feedback sheets being considered in the evaluation, regardless of whether they participate in the voluntary network meetings. This approach will help avoid biased estimates due to the self-selection of physicians who are more enthusiastic about taking part in the network meetings [28]. Furthermore, we will slightly oversample the informal networks (100 instead 96) in case all physicians in an informal network formally reject the feedback sheets sent by the Regional Association of SHI physicians.

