### Statistical methods

The networks will be identified in an iterative fashion. Patients shared by the office-based physicians will be arranged into a matrix that will be used to generate the network structure. This will subsequently be divided into intervention networks using the modularity optimising multilevel algorithm of the igraph package in R. The indicators for the feedback sheet will comprise the characteristics of the networks and the underlying patient population, which will be summarised using descriptive statistics. The indicators of quality of patient care will be calculated as combined indicators encompassing medication, procedures, use of services and/or (re-)admissions.

For the evaluation, we will analyse differences in the primary and secondary outcomes between the intervention and control groups. Despite randomisation, it is conceivable that the results might be affected by external factors, such as the individual disease risk of patients, itself driven by differences, for example, in demographics [29], compliance [30], socioeconomic factors [31], and the organisation of the hospital sector [32]; this will therefore be adjusted using multilevel regression models with the network as random effect.

Comprehensive sensitivity analyses of the evaluation outcomes are planned, including systematic comparisons of competing models of risk adjustment [33] and different levels of significance.

For the cost-effectiveness analyses, the cost data will be taken from the routine data provided by the three participating statutory health insurers (Techniker Krankenkasse, AOK Rhineland/Hamburg, AOK North West). We will use the German standard cost model and choose the perspective of the statutory health insurers (i.e., the payer perspective) in order to provide information for reimbursement decisions. The primary outcomes of the cost-effectiveness analyses will also be hospital admissions resulting from ambulatory-care-sensitive conditions. The incremental cost-effectiveness ratios (ICER) will be calculated using bootstrapping methods. The statistical uncertainty will be estimated using cost-effectiveness acceptability curves (CEAC).

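### Sixty facilitators serve 100 intervention networks, but the stated outcome model has no facilitator level, so the interval for the treatment effect may be somewhat too narrow

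*Protocol article*

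**What the plan says.** - **Number of networks** (Randomisation and sample size estimation): "we will select a random sample of 100 intervention and 100 control networks".
- **Delivery** (Intervention): physicians in each intervention network are invited "to take part in a series of four voluntary network meetings", and "The meetings will be led by a trained facilitator".
- **Number of facilitators** (Outcomes, process evaluation): "Initially, all 60 facilitators will have to complete a questionnaire".
- **Analysis** (Outcomes): "The outcomes will be evaluated using an intention-to-treat approach within multi-level models". Statistical methods then gives the random-effect structure: "this will therefore be adjusted using multilevel regression models with the network as random effect". The sensitivity analyses announced there concern risk-adjustment models and significance levels, not clustering.
- **Who is analysed** (Randomisation and sample size estimation): all physicians who receive feedback sheets, "regardless of whether they participate in the voluntary network meetings".

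The protocol does not say how facilitators are assigned to networks, whether one person stays with a network for all four meetings, or how much facilitators are expected to differ. The design effect in the sample size section covers network clustering only.

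**The concern.** Sixty people cannot lead the meetings of 100 networks without overlap. Control networks have no facilitator, so this extra clustering exists in one arm only and the design is partially nested.

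A network random effect absorbs whatever a facilitator adds to a single network. It does not absorb the covariance between two networks led by the same person, and the stated model treats those networks as independent. If some facilitators are better than others at engaging physicians or getting a patient pathway agreed, and this carries through to hospitalisations, the variance of the intervention-arm mean is understated.

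What is at stake is the coverage of the interval for the primary effect. The protocol means to use the results when discussing whether the intervention could be implemented in other contexts within Germany. Other facilitators would presumably deliver it there, so variation between facilitators is part of the relevant uncertainty.

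**Working it through.** **Inputs from the protocol:** 100 networks per arm, 60 facilitators, ICC 0.015, 300 patients per network, expected rates 20% and 17%, two-sided 5% level.

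**Assumed, not in the documents:** f, the share of between-network variance in the intervention arm that is due to facilitators; one facilitator per network; equal total between-network variance in both arms.

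**1. The plan's own figures.** The two-sided comparison of 20% with 17% at 80% power, without continuity correction, gives 2629 patients per group, as stated. The design effect is 1 + 299 × 0.015 = 5.485, as stated. Neither has a facilitator term.

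**2. Amount of sharing.** 100 / 60 = 1.67 networks per facilitator on average. Let M be the sum of squared loads divided by 100.
- Most even load, 40 facilitators with two networks and 20 with one: M = (40 × 4 + 20 × 1) / 100 = 1.8. Here 80 of the 100 networks share a facilitator.
- A less even load, 20 with three and 40 with one: M = (20 × 9 + 40 × 1) / 100 = 2.2.

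**3. Variance of a network mean**, in units of p(1 − p): 0.015 + 0.985 / 300 = 0.01828. The between-network part is 0.015 / 0.01828 = 0.820 of this. The rest is sampling variance within networks, which facilitators do not affect.

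**4. Variance that the network-only model omits.** The true variance of the intervention-arm mean, divided by the modelled one, is A = 1 + (M − 1) × f × 0.820. The ratio of true to modelled standard error of the arm difference is R = √[(1 + A) / 2]. A nominal 95% interval misses the true effect with probability 2[1 − Φ(1.96 / R)].

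| f (assumed) | R, M = 1.8 | Miss rate | R, M = 2.2 | Miss rate |
|---|---|---|---|---|
| 0 | 1.000 | 5.0% | 1.000 | 5.0% |
| 0.05 | 1.008 | 5.2% | 1.012 | 5.3% |
| 0.10 | 1.016 | 5.4% | 1.024 | 5.6% |
| 0.20 | 1.032 | 5.8% | 1.048 | 6.1% |
| 0.50 | 1.079 | 6.9% | 1.116 | 7.9% |

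Example, f = 0.50 and M = 1.8: A = 1 + 0.8 × 0.5 × 0.820 = 1.328; R = √(2.328 / 2) = 1.079; 1.96 / 1.079 = 1.817; miss rate 6.9%.

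**5. Which f is plausible.** At a 17% rate the between-network variance is 0.015 × 0.17 × 0.83 = 0.00212, an SD of 4.6 percentage points. The facilitator SD is √f times this: 1.0 point at f = 0.05, 1.5 at 0.10, 2.1 at 0.20 and 3.3 at 0.50. The whole expected effect is 3 points, so f = 0.50 would need facilitators to vary by more than the intervention is expected to achieve.

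**6. Larger networks.** The abstract gives 1.9 million patients. If they were spread evenly over 200 networks and only the 41.49% covered by the three insurers were analysed, each network would have about 3,940 patients. The factor 0.820 would rise to 0.984, and the miss rates at f = 0.50 to 7.3% and 8.5%.

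**The case against.** Several objections limit the size of the problem, and most of them stand.

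- **No facilitator effect is documented.** Facilitators receive common training and a manual, which should narrow their differences. If facilitators rotate between networks, the shared component is diluted further.
- **The effect on the outcome is diluted.** Meetings are voluntary, feedback sheets do not depend on the facilitator, and every physician sent a sheet is analysed. This points to small f.
- **The network is the randomised unit.** If the intervention changes nothing in any network, randomisation keeps the test valid. That protects only this strict null. It does not protect interval coverage when effects vary by facilitator.
- **A facilitator variance may not be estimable.** In a simulation of the most even load with an ANOVA estimator, the estimate was zero or negative in about 31% of trials at f = 0.10 and 40% at f = 0.05. The added level would often leave the result unchanged.
- **An analysis plan not shown might add this level.** That is possible. The article does, however, state the random-effect structure, and the structure it states leaves out a level that the design creates.

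A reader might infer that the intervals are certainly too narrow, or that the trial loses its power. The documents support neither. The first needs a facilitator variance above zero, and no figure for it is given. On the second, 100 networks per arm give about 98% power on the stated inputs, and still about 94% at the most even load if all between-network variance came from facilitators.

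**Conclusion.** The point holds in conditional form. Sharing of facilitators in the intervention arm follows from the protocol's own counts, provided that all networks meet, and the stated model has no term for it. If facilitators differ in their effect on hospitalisations, precision is overstated. The table gives the size: from nothing to a standard error about 8% too small at the most even load, and about 12% at the less even one.

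These figures rest on an assumed f of 0 to 0.50, 300 patients per network and one facilitator per network. The lower rows are the more plausible. Actual loads are not stated, and more uneven ones would raise the figures. The matter concerns interval coverage rather than power and is worth correcting because the correction is cheap. It does not invalidate the planned analysis.

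**What to change.** Obtain from the Regional Associations, whose coordinators organised the meetings, which facilitator led each network's meetings. In Statistical methods, add a facilitator level in the intervention arm only, each control network being its own unit. This can be a partially nested random effect, or a cluster-robust variance with the facilitator as the top unit in that arm. Where a network had several facilitators, fix in advance how it is classified, for example by whoever led most of its meetings, or by multiple membership. At the least, pre-specify this as a sensitivity analysis beside the network-only model.

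The cost is a slightly wider interval, a variance component that may be estimated as zero, and one extra identifier to link to the analysis data. The data flow described under Data management mentions no facilitator identifier, so the linkage needs to be arranged before the analysis.

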## Discussion

Although many researchers have focused on identifying informal networks [34–36], this will be the first randomised, controlled study to (a) provide physicians within such networks with structured feedback on network characteristics and patient care based on an analysis of routine data and (b) invite these physicians to facilitated, face-to-face meetings in which they can exchange information and views on the coordination of care in the German ambulatory sector. The approach that will be taken in our intervention builds on the results of studies suggesting that health outcomes can be improved through regular, informal communication between physicians and agreed treatment pathways, including standards for timely transfer of patient-relevant data [26].

Linking routine data from the Associations of SHI Physicians and the statutory health insurers makes it possible to obtain a bird’s eye view of actual patient care pathways and the care delivered to patients, as well as to identify the physicians who deliver this care and to provide these physicians with information on treatment activity.

There is strong evidence from Cochrane reviews that feedback can improve everyday medical practice by shedding light on previously unknown relationships [12, 13]. Providing physicians with information on how they are connected with their colleagues and what the outcomes are of care delivered within their informal networks can help them make these improvements, as well as strengthen their awareness of possible discontinuities in the care they provide.

A potential limitation of this study is the willingness of office-based physicians to take part in the network meetings. Their voluntary participation is planned to take place in the evenings after their practices have closed. It is uncertain, however, whether the invitations and feedback sheets will suffice as motivation for them to take part in the meetings. In order to address this risk, the Regional Associations of SHI Physicians will publish early information about the intervention in their member newspapers and provide the names of people in the various organisations who can be contacted if their members have further questions about the study. In the process evaluation, we will analyse potential barriers to participation in the network meetings.

## Ethics and dissemination

The protocol was reviewed and approved by the ethics committee of Düsseldorf Medical School (2018/01/22 and 2017/10/24) and by the State Ministry of Employment, Health and Social Affairs in North Rhine Westphalia (2017/11/21), the State Ministry of Social Affairs (2017/09/22), Health, Youth, Families and Seniors in Schleswig Holstein (2017/09/29), the Hamburg Senate for Health and Consumer Protection (2018/02/15) and the Federal Office for Social Security (2017/09/22) in their role as regulatory authorities. Dissemination strategies will include reports, the presentation of results in publications and conferences, and public relations.

## Trial Status

The protocol has the version number 1, dated 11th November 2020, the recruitment began in July 2018 and will be completed by January 2021.

## Data Availability

Dissemination strategies include reports, the presentation of results in peer-reviewed journals and at conferences, and public relations activities in line with the recommendations of the International Committee of Medical Journal Editors (ICMJE). Due to data protection restrictions and regulations only the LMU/TUM will have access to the full dataset.

## Abbreviations

ACSD: Ambulatory-care-sensitive diagnoses
ACSH: Ambulatory-care-sensitive hospitalisation
ASHIP: Regional Associations of SHI Physicians
CEAR: Cost-effectiveness acceptability curves
GKV: Statutory Health Insurance
ICC: Intracluster correlation coefficient
ICER: Incremental cost-effectiveness ratios
LMU: Ludwig-Maximilians-University Munich
SHI: Statutory Health Insurance
VST: Trust Centre
Zi: Central Institute for SHI Physician Care in Germany
TUM: Technical University of Munich
